### 2.3. Exercise Program

The exercise program will begin in a rehabilitation center and continue as a home exercise program. The first three sessions will be supervised by a physical therapist at the center to ensure that patients perform all exercises correctly and learn how to exercise appropriately at home. The physical therapist will be blind to patients’ baseline measurements.

The entire exercise program will last for 3 months, with a frequency of 5–7 times per week. Each session will last between 30 and 45 min.

The objectives of the exercise program are to increase the range of motion in the affected ankle, strengthen the affected ankle muscles, improve stability in the injured lower limb, coordinate both lower limbs, retrain walking, and regain previous recreational abilities (running, jumping, climbing, cycling). The goal of increasing stability is to prevent ankle sprains, as patients with this condition have a high risk of spraining their affected ankle [12].

The program includes exercises for ankle mobility (dorsiflexion, plantar flexion, inversion, and eversion) and strengthening (concentric contractions of the anterior, posterior, and peroneus muscle groups, thera-band (Figure S1), and light ankle sandbags exercises (Figure S3a)) [37]. Patients will also perform walking forward and sidewards (without obstacles and with obstacles), walking backward, and up and down stairs (Figures S4 and S5). The program will also include the use of a wobble cushion (Figure S3b) and single leg exercises to improve balance and ankle stability (Figures S2 and S3c) [37,38].

Patients’ compliance will be assessed using daily registration in a logbook [39]. It is necessary for the patients to keep track of the number of sessions per week and the duration of each session. Compliance will be calculated by dividing the amounts of exercises actually performed by the prescribed amount of exercise (5–7 sessions of exercises per week, 30 to 45 min for each session). Furthermore, participants will record other medical treatments or injuries that occur during the rehabilitation period in the logbook. If participants have a compliance score of less than 50% (i.e., less than 3 exercise sessions per week), they will be excluded from the study.

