#### 2.2.3. Discontinuing Criteria

Any patients who do not use the foot orthosis or fail to comply with the exercise program will be excluded from the study. Also, patients who, during the rehabilitation period, suffer any lower limb injury or any injury that may affect gait or muscle strength will be excluded from the study.

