#### 2.2.4. Interventions

Before the baseline assessment, patients will be divided into two groups. Both groups will undergo an identical exercise program. Group 1 will also wear carbon foot orthoses with full reinforcement specially designed to correct the asymmetries detected on the first set of measurements. Gait parameters analysis can help determine specific movement asymmetries [12,13,14]. The Scheinworks treadmill will be used for this purpose, allowing a practical equilateral overview of important gait parameters [35]. During the analysis, the following parameters were taken into consideration: maximum force exerted by the forefoot and backfoot (expressed as a percentage in relation to body weight); step length (measured in centimeters), which is the distance between the foot contacts on opposite sides of the body; stance phase (expressed as a percentage), which is the period of the gait cycle when the foot is in contact with the ground; swing phase (also expressed as a percentage), which is the period of the gait cycle when the foot is not in contact with the ground; step time (measured in seconds), which is the time between the heel contact of one side of the body and the heel contact of the opposite side; stride time (measured in seconds), which is the time taken for the left and right limbs to complete one stride; step cadence which is the number of steps taken per minute, and velocity (measured in kilometers per hour), which is the speed of gait [12,16,35]. A blueprint or scan of the feet will also be performed. Having determined the correct shoe size, a trial insole will be made to fit the diagnosis. Further corrections can be made if the desired gait pattern has not yet been achieved. In most cases, the insole’s influence should be directly recognizable after a couple of steps. The insoles will be designed for both injured and non-injured side based on patients’ specific needs. The movement cycles can be recorded with patients going barefoot, wearing shoes, or foot orthoses [36]. The carbon element that stiffens the orthosis is narrow, while the cover is wide, allowing for optimal fitting in various shoes without causing damage to the carbon [35], so that patients can wear them every day regardless of the type of footwear used and the type of activity undertaken.

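### Patients can be excluded for not using the orthosis, but the compliance record described covers exercise only, and no measure or threshold of wear is given

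*Protocol article*

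**What the plan says.** All references are to the protocol article.

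- **The contrast between arms (section 2.2.4).** "Both groups will undergo an identical exercise program". The difference is that "Group 1 will also wear carbon foot orthoses with full reinforcement". On how much they are worn, the section says only that their construction suits many shoes, "so that patients can wear them every day regardless of the type of footwear used and the type of activity undertaken". It sets no amount of wear.
- **The exclusion rule (section 2.2.3).** "Any patients who do not use the foot orthosis or fail to comply with the exercise program will be excluded from the study".
- **The compliance record (section 2.3).** In a daily logbook, patients must "keep track of the number of sessions per week and the duration of each session". In addition, "participants will record other medical treatments or injuries that occur during the rehabilitation period in the logbook".
- **The compliance score (section 2.3).** "Compliance will be calculated by dividing the amounts of exercises actually performed by the prescribed amount of exercise". The cut-off follows: "If participants have a compliance score of less than 50% (i.e., less than 3 exercise sessions per week), they will be excluded from the study".

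Orthosis wear is not among the listed logbook contents and is not part of the score. The article mentions no other way of measuring it.

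**The concern.** The trial asks whether orthoses add something to exercise. The article gives a full adherence measure (instrument, formula, cut-off) for the exercise that both arms share, and none for the orthosis that separates them. Yet orthosis use is a condition for staying in the study.

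Two things are at stake. First, patients may leave Group 1 after randomisation under a rule with no stated measurement behind it, and Group 2 has no counterpart. Second, exposure to the tested treatment could not be described at the end. That exposure matters here because gait (section 2.4.1) and strength (section 2.4.3) are described as tested barefoot. For those outcomes any difference between arms has to come from wear accumulated before the test.

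**Working it through.** The plan gives no figure for wear, so the main check sets its provisions side by side. The only figure used is the arm size of 21 (section 2.1), taken as stated.

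**Step 1. Compare the two halves of the exclusion rule.**

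| | Exercise | Orthosis |
|---|---|---|
| Received by | both arms | Group 1 only |
| Prescribed amount | 5–7 sessions a week, 30–45 min each | none stated |
| Recorded in the logbook | sessions and their duration | not listed |
| Score | performed / prescribed | none |
| Cut-off | below 50% | none |
| Consequence of failing | exclusion | exclusion |

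The consequence is the same in both columns. Only the exercise column says how failure is established.

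**Step 2. Who can meet the orthosis condition.** Group 2 is given no study orthosis, so a Group 2 patient cannot fail to use it. Every exclusion on this ground falls on Group 1. Whoever applies the rule therefore knows the allocation of the patient concerned. The blinding of assessors and analysts in section 2 does not protect against selection at this step.

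**Step 3. What removals do to the Group 1 mean.** Let *k* of the 21 Group 1 patients be removed. Let the mean outcome be *m_r* among those retained and *m_x* among those removed.

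- Mean of all 21: [(21 − k) × m_r + k × m_x] / 21
- Retained mean minus full mean: (k / 21) × (m_r − m_x)

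The documents give neither *k* nor the gap *m_r − m_x*, so both are assumptions. As a yardstick only, the last column sets the gap equal to the planning effect size of 0.8 SD (section 2.1).

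| k removed | Share of Group 1 (k/21) | Shift if the gap is 0.8 SD |
|---|---|---|
| 1 | 0.048 | 0.04 SD |
| 2 | 0.095 | 0.08 SD |
| 4 | 0.190 | 0.15 SD |
| 6 | 0.286 | 0.23 SD |

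The shift is zero if removed and retained patients have the same mean outcome. It favours the orthosis if the removed patients did worse and counts against it if they did better.

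**Step 4. What a null result would mean.** If all randomised patients are analysed, a null result estimates the effect of assigning orthoses on top of exercise. Without wear data it cannot show whether the insoles were worn without benefit or were not worn.

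**The case against.** The strongest reply is that this argues from silence in a condensed article. Section 2.3 is headed as the exercise program, so it would naturally describe exercise compliance only. Section 2.2.3 presupposes that someone finds out about orthosis use, and the full protocol or the patient diary may have a field for it. Strictly, the two sections do not contradict each other. Part of this stands: the article does not show that wear will go unrecorded. A reader might infer that exclusions must rest on staff impressions, but the text does not support that, since non-use could, for example, be asked about at follow-up. What remains is that the article did not leave adherence to another document. It set out instrument, formula and cut-off for one half of the rule and nothing for the half that concerns the tested treatment.

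A second reply is that removing patients from one arm after randomisation would be a problem even with perfect wear data. That is correct. Recording wear makes the label checkable, but only keeping non-users in the comparison removes the selection, so the fix needs both parts.

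Two stronger readings are tempting:

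- **A null result could not be interpreted at all.** The documents do not support this. Analysed as randomised, it would still answer a question close to the stated objective.
- **The defect can be expressed as lost power, with the effect shrinking in proportion to wear.** That measures the consequence of patients not wearing insoles. Adding a record would leave every such power figure unchanged. The proportional-dilution assumption has no basis in the documents, and section 2.1 does not state whether the test is one- or two-sided.

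**Conclusion.** The point holds in a limited form. The article makes orthosis use a condition of remaining in the study, describes a compliance record and score that cover exercise only, and states no measure or threshold of wear for the one planned difference between arms. An exclusion that can reach Group 1 alone is therefore not tied to any described data, which allows arm-specific selection.

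Its size cannot be fixed from the documents, because wear and the number of exclusions are unknown. Each removal costs about 4.8% of Group 1. The bias is k/21 of the outcome gap between retained and removed patients, which may be zero. This assumes that exclusion from the study means the patient's outcome does not enter the comparison, which is the plain reading of section 2.2.3. If a fuller document already records wear and keeps these patients in the analysis, a clarifying sentence is enough.

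The loss of interpretation is partial: a null result would still bear on assigning orthoses, but not on wearing them.

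**What to change.** 1. Add a daily wear entry to the existing logbook in both arms: the study insole in Group 1, and any insole of the patient's own in Group 2.
2. Keep these entries away from the blinded assessors and analysts, since they reveal allocation.
3. Reconcile sections 2.2.3 and 2.3, so that any label of orthosis non-use is defined in advance and based on the recorded entry. The clinical decision on continuing the orthosis stays with the investigators and is separate from whether the patient's outcome is analysed.
4. Carry out the 3-month assessment in non-users where possible, and keep them in the primary comparison as randomised.
5. Report wear by arm, and use it only in a supportive adherence analysis defined in advance.

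The cost is one line in a logbook that patients already complete daily, plus some care in handling it. No visit or sample size changes. The downside is that wear is self-reported, as the exercise log already is. The entry has to be in place from the start, because wear during the three months cannot be reliably recovered afterwards.

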### 2.1. Sample Size Calculation

The sample size was calculated using G*Power 3.1.9.7 (Heinrich-Heine-Universität, Düsseldorf, Germany), with a significance level of 0.05, 0.8 power, and an effect size of 0.8. A total of 42 subjects will participate in the study (21 per group) [33].

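### Excluding patients who do not use the insole acts only on Group 1, so intolerance is not carried into the comparison and the logbook as described would not show why they stopped

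*Protocol article*

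**What the plan says.** - **Discontinuing Criteria (2.2.3), device use:** "Any patients who do not use the foot orthosis or fail to comply with the exercise program will be excluded from the study".
- **Discontinuing Criteria (2.2.3), injury:** patients who, during rehabilitation, "suffer any lower limb injury or any injury that may affect gait or muscle strength will be excluded from the study".
- **Exercise Program (2.3), compliance:** "If participants have a compliance score of less than 50% (i.e., less than 3 exercise sessions per week), they will be excluded from the study". The compliance score is built from exercise sessions and minutes; insole wear does not enter it.
- **Exercise Program (2.3), logbook:** patients enter the number and length of their sessions, and in addition "participants will record other medical treatments or injuries that occur during the rehabilitation period in the logbook".
- **Interventions (2.2.4):** only Group 1 gets the carbon-reinforced orthoses. "The insoles will be designed for both injured and non-injured side", and the design is meant so that "patients can wear them every day regardless of the type of footwear used and the type of activity undertaken".
- **Discussion (4):** four kinds of test are made: myotonometry, muscle strength, gait and balance. None measures pain or tolerability.
- **Abstract and Conclusions (5):** the 3-month assessments are to show which of the two treatments does better on muscle properties and tone, gait and balance.
- **Sample Size Calculation (2.1):** "A total of 42 subjects will participate in the study (21 per group"), computed "with a significance level of 0.05, 0.8 power, and an effect size of 0.8".

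**The concern.** The insole is the only thing that differs between the arms. The device-use rule takes patients out after randomisation, on a ground that cannot arise in Group 2. Patients who stop wearing a corrective insole are unlikely to be a random subset, since discomfort, pain on walking or poor fit are plausible reasons. If they leave, Group 1 is reduced to patients who tolerated the device while Group 2 has no matching filter, and the balance created by randomisation is lost.

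Two things are at stake. The first is selection: the functional comparison may favour the insole arm. The second is information: the logbook, as its content is stated, cannot separate a patient who stopped because the insole hurt from one who lost interest. A device that some patients cannot tolerate could then be reported as the better option without the comparison showing it. The Introduction itself counts less pain among the marks of successful treatment.

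**Working it through.** **1. The plan's own figure.** Inputs from section 2.1: effect size 0.8, alpha 0.05, power 0.80, equal arms; the number of sides is not stated. A two-sample t-test (noncentral t) needs 20.03 per arm one-sided, rounded up to 21, or 42 in total. This matches the article. Two-sided it needs 25.52, so 26 per arm, and 21 per arm gives 71.6% power. The present point does not depend on which was meant; 21 per arm serves only as the base for what follows.

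**2. What happens to Group 1 patients with an insole problem under the rules as written.**

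| Situation | Named in the logbook? | In the comparison? |
|---|---|---|
| Untreated discomfort, keeps wearing the insole | No | Yes |
| Untreated discomfort, stops wearing it | No; neither wear nor reason is named | No (device-use rule) |
| Problem treated medically, stops wearing it | Yes, as another treatment | No (device-use rule) |
| Problem counted as a lower limb injury | Yes, as an injury | No (injury rule) |

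Both stopping the insole and a problem serious enough to count as a lower limb injury lead out of the comparison. The injury rule applies to both arms, but an injury caused by the insole can arise only in Group 1.

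**3. Size of the selection effect.** The article gives no rate of non-use, so the inputs here are assumptions: m of the 21 Group 1 patients are removed, and they would on average have scored δ SD worse than those kept, with δ = 0.5 to 0.8.

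Let r = m/21 and let K be the mean of those kept. The mean of all 21 is (1 − r)K + r(K − δ) = K − rδ. Analysing only those kept therefore flatters Group 1 by rδ. Example: m = 4 gives 4/21 × 0.5 = 0.10 and 4/21 × 0.8 = 0.15.

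| Removed (m) | Kept | r | Flattering, δ = 0.5 | Flattering, δ = 0.8 | Power at d = 0.8, one-sided | Two-sided |
|---|---|---|---|---|---|---|
| 0 | 21 | 0% | 0 | 0 | 81.7% | 71.6% |
| 1 | 20 | 4.8% | 0.02 SD | 0.04 SD | 80.8% | 70.4% |
| 2 | 19 | 9.5% | 0.05 SD | 0.08 SD | 79.9% | 69.2% |
| 4 | 17 | 19.0% | 0.10 SD | 0.15 SD | 77.7% | 66.5% |
| 6 | 15 | 28.6% | 0.14 SD | 0.23 SD | 75.0% | 63.3% |

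Power is computed with Group 2 kept at 21. Relative to the planned effect of 0.8, the flattering runs from 0.024/0.8 = 3% to 0.229/0.8 = 29%. The loss of power is modest. The bias matters more, because it goes one way whenever those who stop would have done worse.

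**The case against.** The strongest reply is that this is a condensed article. Adverse-event forms, reasons for withdrawal and the reporting of harms are commonly left to the full protocol. That stands: a reader might infer that the trial collects no harms at all, and the article does not support this. It nowhere says that harms or reasons for stopping will not be noted.

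Three further stronger readings also fail.

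- **That skin damage or pain from the insole goes unrecorded.** Skin damage can be entered as an injury, and a treated problem as another treatment. Only untreated discomfort is clearly outside the stated wording.
- **That affected patients vanish from the report.** The article says they are excluded; it does not say they go uncounted. The flow chart is not shown and may list them. The promised conclusion is also limited to function and is not framed as a balance of benefit and harm.
- **That Group 1 must wear the insole every day.** Section 2.2.4 says only that the design allows it.

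A reader might also put an upper confidence limit on zero events among the patients kept. That has no meaning here: the event rate would be invented, the patients kept may have discomfort too, and untreated discomfort is not recorded as described.

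What survives is the part that rests on a stated rule. Section 2.2.3 excludes non-users, the rule can reach one arm only, and more detail elsewhere would not undo it unless that detail contradicted it.

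**Conclusion.** The point holds in a limited form. Followed as written, section 2.2.3 makes the comparison one between Group 1 patients who tolerated the insole and a Group 2 that faces no such filter. The logbook content in section 2.3 names neither wear nor the reason for non-wear, so intolerance would not be visible from it.

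The direction, in favour of the insole arm, assumes that patients who stop would on average have done worse than those who continue. If they would have done equally well there is no bias in the mean, only a loss of patients. The size is unknown: 0.02 to 0.23 SD for 1 to 6 removals is an illustration under assumed inputs. The documents show no safety signal, and nothing here says that the insole is poorly tolerated. The correction is still worth making, because it is cheap and bears directly on the question the trial asks.

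**What to change.** 1. **Section 2.2.3:** separate stopping the insole from leaving the study. State that all randomised patients are assessed at 3 months where possible and analysed in their allocated group whatever their insole use. Bring the injury rule and the compliance exclusion in section 2.3 into line with this. Without this step a better logbook leaves the selection bias in place.
2. **Section 2.3, logbook, both arms:** add foot, ankle or leg pain or skin problems, with side and date.
3. **Section 2.3, logbook, Group 1:** add insole wear and, when it is not worn, the reason.
4. **Reporting:** show these entries and all discontinuations by arm, for all allocated patients including those who stop, alongside the efficacy results.

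The cost is slightly more burden for patients who already keep a daily logbook, 3-month visits for some patients who would otherwise have left, and one more table. The estimated insole effect may be somewhat diluted by non-wearers; if the effect among wearers is also of interest, it can be shown as a supplementary result. None of this changes how any patient is treated.

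### The compliance score that decides exclusion has no fixed unit or denominator, and its 50% cut-off disagrees with its three-session explanation under several readings

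*Protocol article*

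**What the plan says.** Section 2.3 of the protocol article sets the prescription as two ranges: "The entire exercise program will last for 3 months, with a frequency of 5–7 times per week", and "Each session will last between 30 and 45 min". Patients keep a logbook in which they must "keep track of the number of sessions per week and the duration of each session".

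The score is defined in the same section: "Compliance will be calculated by dividing the amounts of exercises actually performed by the prescribed amount of exercise", and the prescribed amount is spelled out in brackets as "5–7 sessions of exercises per week, 30 to 45 min for each session". The consequence follows: patients with a "compliance score of less than 50% (i.e., less than 3 exercise sessions per week), they will be excluded from the study".

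Section 2.2.3 repeats the consequence without a number: patients who "fail to comply with the exercise program will be excluded from the study". Section 2.3 therefore holds the only numerical threshold. Section 2.1 sets the trial at 42 patients, 21 per group.

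**The concern.** A ratio to a range is not a single number, yet a hard cut-off is applied to it. The sentence then offers a session count as another way of stating the same cut-off. Duration is logged and named as part of the prescribed amount, but it drops out of that session count. If the two criteria select different patients, whoever applies the rule has to choose between them, and the article gives no basis for the choice.

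This is more than a descriptive adherence figure, because the score decides whether a randomised patient stays in the trial. With 21 per group, each exclusion removes 1/21 = 4.8% of an arm, and it does so after randomisation, on behaviour that may itself relate to outcome.

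**Working it through.** **Inputs** (all from Section 2.3): 5 to 7 sessions per week; 30 to 45 min per session; score = amount done / amount prescribed; removal below 50%, explained as fewer than three sessions a week.

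**1. Reproducing the stated equivalence.** At the midpoint of 6 sessions, 3/6 = 50%. Fewer than three sessions is then exactly a score below 50%, so the article's figure reproduces here.

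**2. Sessions as the unit, across the prescribed range.** Half of the prescription is 5/2 = 2.5, 6/2 = 3.0 and 7/2 = 3.5 sessions.

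- At 5, whole sessions in one week: 2/5 = 40% is out and 3/5 = 60% is in. The cut-off is the same as the session count.
- At 5, averaged over the 3 months: a mean of 2.5 to under 3 per week scores 2.5/5 = 50% to under 3/5 = 60%. The score keeps this patient and the session count removes them.
- At 7: 3/7 = 42.9%. The score removes a patient doing three sessions and the session count keeps them.

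**3. Minutes as the unit.** The weekly prescription runs from 5 × 30 = 150 min to 7 × 45 = 315 min, with midpoint 6 × 37.5 = 225 min.

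| Done in a week | of 150 min | of 225 min | of 315 min | By session count |
|---|---|---|---|---|
| 3 × 30 = 90 min | 60.0% | 40.0% | 28.6% | kept |
| 2 × 45 = 90 min | 60.0% | 40.0% | 28.6% | removed |
| 3 × 45 = 135 min | 90.0% | 60.0% | 42.9% | kept |
| 5 × 30 = 150 min | 100.0% | 66.7% | 47.6% | kept |

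The criteria disagree in both directions. Two 45-min sessions pass the score against the minimum but fail the session count. Three 30-min sessions pass the session count but fail the score, even at the midpoint.

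**4. The extreme corner.** A patient doing the full prescribed minimum scores 150/315 = 47.6%. This requires minutes as the unit and the upper bound of both ranges as the denominator. Relaxing either bound to its midpoint takes the score above 50%: 150/(6 × 45) = 150/270 = 55.6%, and 150/(7 × 37.5) = 150/262.5 = 57.1%. By session count the same patient scores 5/7 = 71.4% to 5/5 = 100%.

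**The case against.** The strongest defence is that the explanation in brackets is the operative rule: fewer than three sessions a week. It follows from the natural centre of the range, gives the same whole-session weekly cut-off at 5, and settles every case in the table. A condensed article may also leave the logbook algorithm to a fuller document.

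Much of this stands. A reader might infer that the sentence flatly contradicts itself; it does not, because the two halves agree at 6 sessions and, within a week, at 5. A reader might also infer that patients who do all of the prescribed minimum will be excluded. The article does not support that: it never names 7 × 45 min as the denominator, and its own session count would keep a patient doing five sessions. Nor does the article announce adherence figures by arm, so no claim about such figures is made here.

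The defence does not remove the problem. It works only by setting aside the formula and the recorded durations, which the article itself prints as the definition. The point concerns a formula, a denominator and an equivalence that are all in the text and do not agree, so it is not a detail left to another document.

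It can also be said that handling of excluded patients is a separate matter from the arithmetic, and that the exercise rule is the same in both groups. The first is fair as far as it goes, but the score's only stated use is to exclude, so the two have to be settled together. On the second, a common rule does not guarantee equal removal, since wearing an orthosis could change how much patients exercise.

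**Conclusion.** The concern holds in a limited form. The score is underdetermined, and it conflicts with its own explanation at 7 sessions, at 5 sessions when averaged over the 3 months, and under several minutes readings, including the midpoint. For one week of three 30-min sessions it ranges from 60% to 28.6%, so the same patient can be kept or removed.

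This rests on reading the bracketed ranges as the denominator, as the text does. The choice of unit, point in the range and averaging period is not given, so the alternatives are shown as a range. How many patients would fall in the disputed zone cannot be estimated from the article. The issue matters because the rule acts after randomisation in a trial of 42, where excluding low-compliance patients can bias the between-group comparison.

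**What to change.** In Section 2.3, reconcile the percentage and the session count into a single criterion. State one unit (sessions or minutes), one fixed denominator for every patient, and one averaging period. Which threshold applies is for the investigators.

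In Sections 2.2.3 and 2.3, use that score to define a per-protocol set for a sensitivity analysis. Keep all randomised patients with follow-up in the primary between-group comparison, whatever their score.

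The definition costs about a sentence, and the logbook already records both sessions and minutes. The analysis change means a little more analysis work and continued follow-up of low-compliance patients. It may also dilute the effect estimate, which the per-protocol analysis would help readers judge.
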